### Outcome measures

#### Primary outcome measures

As primary outcome measures at GP level we use the registration of patients’ employment in the electronic medical record (EMR) and the use GPs make of the code Z05 (for work related problems) of the International Classification of Primary Care (ICPC). For each participating GP we establish the percentage of the working age patients for whom the occupation is recorded anywhere in the EMR and we count the instances in which they made use of code Z05. The registration of employment and use of code Z05 in the 6 months following the training will be compared between intervention and control group practices.

The primary outcome measure at patient level is the work-related self-efficacy, measured by the 11 item Return-to-Work Self-Efficacy scale ( RTW-SE) [22]. This scale measures the extent to which people feel able to handle the demands of their job on a scale which ranges from 1 to 6. The RTW-SE is validated and reliable and has a high internal consistency. It was found to strongly correlate to return to work in a sample of sick listed workers; it was also shown to be sensitive to changes in the clinical condition of patients suffering from mental health problems [23].

Outcome measures regarding gender are the use of code Z05 and the registration of occupation in women and men. Moreover we will analyse the score on the RTW-SE scale and investigate its relation to gender and how this is modified by other patient variables like age, occupation, income, health problems, absenteeism and other patient variables.

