## Methods

### Trial design

The study is a cluster randomised controlled trial using randomisation on practice level to prevent contamination. We will randomise the practices into two groups with a 1:1 allocation ratio. GPs in the intervention group practices will receive the training program, GPs in the control practices will deliver care as usual.

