#### Effect evaluation

The outcomes of the questionnaires will be compared between both groups at the three different measurements. Descriptive statistics will be used to summarise the data and detect outliers, missing values and data entry mistakes. We will describe the categorical variables using frequency tables; for each continuous variable we will calculate minimum, maximum, range, median, mean and standard deviation. The data will be further analysed using a multi level model to assess the influence of the different variables. All analyses will be performed at patient level according to the intention to treat principle, so patients will be regarded as belonging to the intervention group if their GP was allocated to the intervention condition, regardless of whether the GP effectively received the training.

The primary independent variable in the analyses will be the GPs’ exposure to the training: trained GP or control group delivering usual care. The primary dependent variables are their patients’ score on the RTW-SE scale, the number of Z05 codes used by the GPs and the proportion of working age patients for whom the occupation is registered. Effects of the intervention will be checked for effect modification by experience and gender of the GPs. All analyses will be performed with SPSS. Effects on the different outcome variables will be assessed at a significance level of 0.05.

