### Strengths and weaknesses of the study

An important strength of our study is the tailored character of the intervention that is based on the findings of our own focus group research. The training is expected to change the behaviour of GPs by making them more aware of the relationship between work, health and gender. This will enable them to recognize WRP in an earlier stage and this will also help them to use more effective therapeutic strategies.

In many trials regarding work related health problems, interventions aim at reducing sick leave. However a risk of taking sick leave as an outcome measure lies in it defining sick leave as the main problem rather than the conditions and circumstances that it is a result of. By our focus on work per se, including its important positive effects on health and well being, we think we can help GPs to better appreciate the meaning of work for patients. Using the beneficial effects of participation may be better suited to the preferences of GPs and the position of trust they have with their patients than playing a role in sickness certification. Once they acknowledge the important positive influence they can exert in this field for their patients, GPs may be motivated to further take up this task.

Another strength lies in the outcome measures we use. Currently, the registration by GPs of patients’ occupations and work related problems is inadequate. Even motivated GPs often do not know the relevant ICPC codes. This leaves much room for improvement making it more likely to find a significant effect of our intervention. Such an effect will also be relevant as registration of work related problems unequivocally shows that GPs pay attention to work. Improving the registration in the EMR has been subject of a government policy. Incentives are used to motivate GPs for adequate ICPC coding in the EMR. This may further stimulate GPs to use the ICPC codes for work related problems. The use of the RTW-SE scale in a primary health care setting will shed new light on the work-health relation of workers visiting their GP. Even if we do not find any effect on this scale, our data may be invaluable in further developing knowledge about the relationship between return-to-work self efficacy, absenteeism and presenteeism. Moreover, it will offer us insight in the possibilities of this instrument in a primary care setting, for instance as a diagnostic tool.

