A weakness at patient level is the fact that most of the data are collected by self-reported questionnaires. This method is always subject to recall bias. However, since both the intervention- and control group will experience this bias, we do not expect that it will influence the comparison between the groups. Another weakness concerns the selection of patients. Only patients who are willing to participate are included This means our findings may not be transferable to all working patients. This effect is expected to occur in comparable ways in both groups.

A weakness at the GP level is the selection of GPs who are willing to participate. We assume that these GPs will be more open to new ideas and more positive concerning work-related issues. This may result in a smaller effect as there will be less room for improvement in the selected group. On the other hand, implementation of the programme amongst GPs in general is assumed to lead to a smaller effect. Heterogeneity of the group of GPs may be another problem. As work gets little attention during the vocational training and in quality improvement schemes of GPs, no ‘standard’ way of dealing with it has evolved. Therefore we expect to find a considerable inter-GP variation which, in its turn, can make it harder to reliably assess the effect of the training intervention.

We think that our study can mean an important step forward in health professionals paying more attention to work. This can lead to more effective and efficient health care for workers.

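### The primary occupation outcome leaves open whether entries made before the training count; if they do, an unadjusted comparison can lose much of its power

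*Protocol article*

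**What the plan says.** All statements are in the protocol article.

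- *Primary outcome measures* defines the occupation outcome for each GP as the "percentage of the working age patients for whom the occupation is recorded anywhere in the EMR". The numerator carries no date, and the denominator is all working-age patients.
- The sentence that follows gives a period: "The registration of employment and use of code Z05 in the 6 months following the training will be compared between intervention and control group practices".
- *Effect evaluation* lists among the primary dependent variables "the proportion of working age patients for whom the occupation is registered", with no period and no pre-training covariate.
- *Strengths and weaknesses of the study* describes the starting level in words only: "Currently, the registration by GPs of patients’ occupations and work related problems is inadequate". It adds: "This leaves much room for improvement making it more likely to find a significant effect of our intervention". On heterogeneity it says: "Therefore we expect to find a considerable inter-GP variation".
- *Trial design* fixes allocation by practice: "We will randomise the practices into two groups with a 1:1 allocation ratio". *Sample size* requires at least 12 GPs per group.

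**The concern.** The defining sentence and the analysis section describe a stock: the share of patients who have an entry, whenever it was made. The comparison sentence describes a flow: registration during 6 months. Two analysts could extract different numbers from the same records, and both could defend their reading. This is a primary outcome, so the choice should not remain open.

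The choice matters because an entry that predates the training cannot be an effect of it. On the cumulative reading, such entries do two things. They remove patients in whom the training could still change anything, which dilutes the contrast. They also carry each GP's past recording habits into a comparison of about 12 with 12. A real improvement could then be missed, although the same records hold the pre-training percentage that would remove most of this variation.

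**Working it through.** **The plan's own figure.** The sample size reproduces. A difference of 0.57 with SD 1.14, 80% power and two-sided alpha 0.05 needs 63 patients per arm. The design effect is 1 + (30 − 1) × 0.15 = 5.35. Then 63 × 5.35 = 337, and 337 / 30 = 11.2, rounded up to 12 GPs. Recruiting 40 leaves 30 after a 25% loss. This calculation is for the RTW-SE. No power is stated for the occupation outcome.

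**Dilution.** Let b be the pre-training share with an entry and g the share newly registered among those without one. The cumulative percentage is b + (1 − b)g, so the arm difference is (1 − b)(g₁ − g₀). A 10-point gain becomes 9.5 points at b = 5%, 8 at b = 20% and 5 at b = 50%.

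**Power on the cumulative reading.** The article gives none of the following inputs, so all are assumptions:

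- 12 v 12 GPs, each treated as an independent cluster, with 1,000 working-age patients per GP
- 60% consult in the window
- new registration among consulting patients without an entry: 12% v 5% (mean 8.5%)
- between-GP SD in that rate: 4 points
- b and its between-GP SD s varied

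Formulas, in percentage points:

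- difference = (1 − b) × 0.6 × 7
- variance = [s × (1 − 0.6 × 0.085)]² + [(1 − b) × 0.6 × 4]² + sampling variance (SD about 0.6 to 0.7)
- noncentrality = difference / (SD × √(2/12)), t-test with 22 df

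Example at b = 20%, s = 8: the difference is 0.8 × 0.6 × 7 = 3.36. The components are 7.59, 1.92 and 0.62, so the SD is 7.86. Noncentrality is 3.36 / (7.86 × 0.408) = 1.05, and power is 0.17.

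| b | s (points) | Difference | SD | Power, formula | Power, simulated |
|---|---|---|---|---|---|
| 5% | 2 | 3.99 | 3.04 | 0.87 | 0.84 |
| 10% | 3 | 3.78 | 3.63 | 0.68 | 0.65 |
| 10% | 5 | 3.78 | 5.26 | 0.39 | 0.39 |
| 20% | 3 | 3.36 | 3.49 | 0.62 | 0.57 |
| 20% | 5 | 3.36 | 5.16 | 0.33 | 0.33 |
| 20% | 8 | 3.36 | 7.86 | 0.17 | 0.16 |
| 20% | 12 | 3.36 | 11.57 | 0.10 | 0.11 |

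**With the pre-training percentage as a covariate.** The first variance component drops out. At b = 20% the SD becomes √(1.92² + 0.62²) = 2.02, noncentrality is 3.36 / (2.02 × 0.408) = 4.08, and power is about 0.97. Simulated power is about 0.95 to 0.97 in every row. Counting only new entries among all patients without one, whether or not they consult, gives about 0.96.

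**A larger assumed effect.** Take new registration of 2% v 12% of all patients without an entry, with a between-GP SD of 3 points. Unadjusted power is then about 1.00 at b = 5% (s = 2), 0.95 at 20% (s = 5), 0.50 at 20% (s = 10) and 0.13 at 50% (s = 15). Counting new entries only gives about 1.00.

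**The case against.** The strongest reply is that the word *anywhere* names a place in the record, not a period, and that the next sentence supplies the period. Read together, the two sentences can mean entries made in the 6 months, wherever they sit. A reader might infer from the definition alone that all earlier entries are included. The documents do not establish that, and this part of the reply stands. It does not remove the ambiguity, because the defining sentence and *Effect evaluation* both omit the window. Even on the new-entry reading, the stated denominator still includes patients who already have an entry.

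A reader might also infer that old registrations must swamp the effect. That is not shown. The article gives no baseline percentage, calls current registration inadequate, and so points to a low level. Its remark on variation between GPs concerns ways of dealing with work in general, not the occupation percentage. With a low and uniform baseline the loss is modest. With a moderate or uneven one it is large.

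Two further limits stand. Old entries do not bias the comparison: randomisation by practice leaves dilution and chance imbalance only. And an article may leave covariates to a full analysis plan, so a missing baseline adjustment would not be a finding by itself. The finding is the unresolved definition. The Z05 outcome is not affected in the same way, since it reads as a count within the stated window.

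**Conclusion.** The point holds as an unresolved definition of a primary outcome with a possible, and possibly large, loss of power. The text does not say whether pre-training entries count, and it names no pre-training value. On the cumulative reading, unadjusted power under the main assumed effect runs from about 0.84 (baseline 5%, SD 2 points) to about 0.1 (baseline 20%, SD 12). With adjustment it is about 0.95 to 0.97. These figures rest wholly on assumed inputs; what they show is the direction of the loss and how strongly it depends on the spread of the pre-training percentage. On the new-entry reading the loss largely disappears, but the denominator still needs stating. The comparison is valid on either reading.

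**What to change.** Reconcile *Primary outcome measures* with *Effect evaluation* by adopting one of two definitions:

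1. **New entries.** Among working-age patients listed without an occupation at the training date, report the proportion with one recorded 6 months later. Use the same calendar window in control practices, which have no training date of their own in that period. Do not restrict the denominator to patients who consult afterwards, because the training could affect who consults.
2. **Cumulative percentage.** Keep all entries, say so, and include each GP's pre-training percentage as a covariate in the model.

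If entries are not dated in the record, take one extract at the training date and one 6 months later. Adjusting Z05 use for the preceding 6 months is an optional gain in precision.

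The cost is one additional EMR extract per practice and, for the second option, one covariate. No patient contact is needed.

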### Randomisation

We aim to recruit at least 24 GPs who will be randomised into an intervention group and a control group. To prevent contamination, we will randomise clusters on practice level. A statistician will generate a block randomisation scheme using a block size of 2 and practices will be assigned to either condition according to the order in which they are recruited. After this order is established the allocation of the random sequence will be performed by the researcher.

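### Z05 use is compared only after training, without each GP's own earlier Z05 count; with about 24 GPs this can cost precision, though it does not bias the comparison

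*Protocol article*

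**What the plan says.** Under Primary outcome measures, Z05 use is a count for each GP: "we count the instances in which they made use of code Z05". The window and the contrast follow: "The registration of employment and use of code Z05 in the 6 months following the training will be compared between intervention and control group practices". Under Effect evaluation, exposure to the training is the primary independent variable, and the primary dependent variables include "the number of Z05 codes used by the GPs and the proportion of working age patients for whom the occupation is registered". A multilevel model is announced without a list of covariates. GP experience and gender are named, but only as possible effect modifiers. A pre-training Z05 count, a change score or a baseline covariate appears nowhere.

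On size and allocation, the Randomisation section says "We aim to recruit at least 24 GPs who will be randomised into an intervention group and a control group" and "To prevent contamination, we will randomise clusters on practice level". Allocation is 1:1, and "A statistician will generate a block randomisation scheme using a block size of 2", applied in order of recruitment. No stratification is mentioned. In the Discussion the authors write: "Therefore we expect to find a considerable inter-GP variation which, in its turn, can make it harder to reliably assess the effect of the training". The sample size section concerns the RTW-SE scale; no power or effect size is given for Z05.

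**The concern.** Use of a rarely taught code probably differs between GPs for reasons unrelated to the training. If a GP's habit is stable, the count from an earlier period predicts the later one, and adjusting for it removes that part of the error. Z05 suits this well. The count comes from the EMR, so an earlier period should be obtainable from the same source, and entries made before the training cannot be affected by it. The patient questionnaires offer no such baseline, because the first is completed after the consultation, and inclusion starts only after the GPs are trained.

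Nothing else in the design controls earlier coding: blocks of two in recruitment order do not balance it. With about 24 GPs, a real change in coding could be missed because between-GP variance swamps it.

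**Working it through.** **1. The plan's own figure.** The sample size section uses an SD of 1.14, a difference of half an SD (0.57), 80% power, alpha 0.05 (two-sided assumed), an ICC of 0.15 and 30 analysed patients per GP.

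- Per arm without clustering: 2 × (1.960 + 0.842)² / 0.5² = 62.8, so 63.
- Design effect: 1 + 29 × 0.15 = 5.35.
- 63 × 5.35 = 337 patients; 337 / 30 = 11.2, so 12 GPs per arm.
- 30 / 0.75 = 40 patients recruited per GP.

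The stated 12 GPs and 40 patients reproduce, but for RTW-SE only.

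**2. Post-only comparison of Z05.** Treat each GP as one independent unit, with k = 12 per arm and a difference of d between-GP SDs. The t-test has 2k − 2 = 22 df and noncentrality d × √(k/2). Power of 80% needs d = 1.197: noncentrality 1.197 × √6 = 2.93, critical value 2.074, power 80.0%. So the comparison detects only a difference of about 1.2 between-GP SDs.

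**3. With the GP's own earlier count as covariate.** The df fall to 2k − 3 = 21. The residual variance is multiplied by (1 − rho²), and by 1 + 1/(2k − 4) = 1 + 1/20 for chance imbalance in the covariate. The noncentrality is 1.197 × √6 / √[(1 − rho²) × 1.05]. At rho 0.5 it is 2.932 / √(0.75 × 1.05) = 3.30. Rho is an assumption throughout.

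| rho | Variance factor 1 − rho² | Power | Change from 80.0% |
|---|---|---|---|
| 0 | 1.00 | 77.9% | −2.1 points |
| 0.3 | 0.91 | 81.6% | +1.6 |
| 0.5 | 0.75 | 88.3% | +8.3 |
| 0.7 | 0.51 | 96.8% | +16.8 |

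The gain passes 5 points at a rho of about 0.42.

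**4. Practices as the units.** The number of practices is not stated. The same formulas with d = 1.197 and assumed numbers of practices give:

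| Units per arm | Post-only | Adjusted, rho 0 | Change |
|---|---|---|---|
| 12 | 80.0% | 77.9% | −2.1 points |
| 8 | 60.6% | 56.7% | −3.9 |
| 6 | 46.6% | 41.6% | −5.0 |

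With 8 per arm and rho 0.3 there is neither gain nor loss (60.6% and 60.7%).

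**5. What rho might be.** Simulated Poisson counts with gamma-distributed GP effects (12 GPs per arm, square-root scale, 4,000 runs, a doubling under training) show how far this depends on the usual count. All inputs are assumed.

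| Mean Z05 count per 6 months | Between-GP CV | Pre/post correlation | Power post-only | Power adjusted |
|---|---|---|---|---|
| 0.5 | 0.5 | 0.10 | 22% | 21% |
| 1 | 0.5 | 0.18 | 35% | 35% |
| 1 | 1.0 | 0.46 | 21% | 26% |
| 3 | 0.5 | 0.40 | 61% | 68% |
| 3 | 1.0 | 0.71 | 28% | 53% |
| 10 | 1.0 | 0.89 | 29% | 90% |

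With one code or fewer per half-year and moderate variation between GPs, the covariate does nothing. With several codes and wide variation it helps greatly.

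**The case against.** **The article does not rule out adjustment.** It fixes a window and a contrast, and an adjusted model also compares post-training use between arms. The multilevel model has no covariate list, and articles commonly leave that to a fuller plan. This stands in part: a fuller plan may contain the covariate. But the outcome definition names only a post-training window, and a baseline count has to be extracted before it can be used.

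**The gain may be small.** This stands. The Discussion calls current registration inadequate and says that even motivated GPs often do not know the codes. That points to low counts and a low rho, and nothing in the article supports 0.5 as a default. The authors also expect much room for improvement. If the effect is larger than 1.2 SD, less is at stake: at rho 0.5 the gain is 3.7 points at d = 1.5 (93.9% to 97.6%) and 1.2 points at d = 1.75 (98.4% to 99.6%).

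**Stronger readings that the article does not support.** A reader might infer that a pre-existing difference in coding could pass for a training effect. That is chance imbalance, which a valid test under randomisation already covers within its 5% error rate; it is not bias. A reader might also take the authors' remark on inter-GP variation as evidence of stable differences in Z05 rates. It concerns ways of dealing with work in general, so it makes such differences plausible without measuring them. Nor can the possible loss be put at 2 points at most: that holds only if every GP forms a separate practice.

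**Access to earlier records is inferred.** The article does not describe historical extraction or how codes are attributed to individual GPs.

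**Conclusion.** The point holds as one of efficiency. The Z05 comparison as written uses only post-training counts, so any stable between-GP difference in coding remains in the error. The test stays valid.

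The size cannot be fixed from the article. With 12 independent units per arm and an effect of 1.197 SD, the change in power from adjusting runs from about −2 points at rho 0 to about +17 at rho 0.7. It is about nil if Z05 is hardly used before training. With fewer practices than GPs, the possible loss is 4 to 5 points under the assumed 8 or 6 per arm. The case for the change rests on its low cost and on a possible gain larger than the possible loss, not on a demonstrated gain.

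**What to change.** Under Primary outcome measures, add a Z05 count for each GP over a fixed period before the training date, with the same calendar window for control GPs. Six months would match the outcome window; a longer period, such as 12 months, is better if codes are rare. First confirm that the EMR query can reach back and attribute codes to GPs.

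Under Effect evaluation, prespecify a count model for the post-training Z05 count, with the pre-training count as covariate (for example as log(count + 0.5)), that accounts for the practice as the unit of randomisation. Keep the unadjusted comparison as a sensitivity analysis. Settle this before outcome data are seen.

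The cost is one earlier extraction window and one degree of freedom, with the power risk stated above if earlier use proves uninformative. No extra patients, visits or questionnaires are needed.
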